### Sample size calculation

The null hypothesis is that WI is inferior to WI plus L-TAP. To test the alternative hypothesis of noninferiority of WI compared with WI plus L-TAP, the sample size is calculated using the mean value of NRS. Considering our results with previously treated patients, the mean (standard deviation [SD]) pain intensity score according to NRS is 2.8 (1.9) for the WI plus TAP block group and 3.1 (1.9) for the WI group. These data have been used for the sample size calculation. The noninferiority limit of NRS 1 has been intended to be the largest difference that is clinically acceptable, so that a difference greater than 1 would matter in practice. A two-sided sample size calculation with 0.8 power and significance level of 0.05 reveals that 100 patients have to be included. With an estimated dropout rate of 8%, a sample size of 108 patients is required with 54 patients in the WI group and 54 patients in the WI plus L-TAP group. Patient recruitment is split between the two centers. Sample size has been calculated using PASS® version 14.0.8 with a noninferiority test for the difference of two means.

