**Methods/design:**

This is a prospective, randomized, controlled, two-arm, multicenter, single-blind study evaluating the efficacy of postoperative analgesic management of WI versus WI plus L-TAP in the context of laparoscopic colorectal surgery. Randomization is at the patient level, and participants are randomized 1:1 to receive either WI alone or WI plus L-TAP. Those eligible for inclusion were patients undergoing laparoscopic resection for colorectal tumor or diverticular disease at the Division of General and Hepatobiliary Surgery, Verona University, Verona, Italy, and at the Colorectal Cancer Center, Kyungpook National University, Daegu, Korea. Fifty-four patients are needed in each group to evidence a difference greater than 1 of 10 according to the numeric rating scale for pain assessment to establish that this difference would matter in practice.

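### The inputs stated for the sample size do not give 80% power with 100 patients; at a 0.3-point difference and a 95% CI the power is about 45%

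*Protocol article*

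**What the plan says.** All the inputs are in one paragraph of the protocol article, Sample size calculation.

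- **Means and SD:** "2.8 (1.9) for the WI plus TAP block group and 3.1 (1.9) for the WI group", followed by "These data have been used for the sample size calculation".
- **Margin:** "The noninferiority limit of NRS 1 has been intended to be the largest difference that is clinically acceptable".
- **Method:** a "noninferiority test for the difference of two means", run in a named commercial package.
- **Result:** "A two-sided sample size calculation with 0.8 power and significance level of 0.05 reveals that 100 patients have to be included". This is raised to 108 (54 per arm) for 8% dropout.

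The Abstract (Methods/design) repeats the requirement: "Fifty-four patients are needed in each group to evidence a difference greater than 1 of 10". The Statistical analysis section bases the noninferiority decision on a 95% confidence interval, which agrees with two-sided 0.05, that is, one-sided 0.025 at the margin.

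**The concern.** A higher score means more pain, and WI is the arm to be shown noninferior. The assumed means therefore place WI 0.3 points on the wrong side of zero, and only 0.7 of the 1-point margin is left to detect. With SD 1.9, 50 patients per arm is few for a distance of 0.7.

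If the power is overstated, the chance of a positive result on the primary endpoint is overstated too. The article says that a demonstration of noninferiority would call the role of TAP block into question. A reader who trusts the 80% could take a failed test as a sign that L-TAP adds benefit, when imprecision would be a likely explanation.

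**Working it through.** **Inputs** (Sample size calculation, except where noted): margin M = 1; assumed difference d = 3.1 − 2.8 = 0.3 against WI; SD σ = 1.9; power 0.80; two-sided 0.05, so one-sided α = 0.025 at the margin; allocation 1:1 (Trial design).

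**Step 1. Patients needed.** The normal approximation is

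n per arm = 2σ²(z₁₋α + z₀.₈)² / (M − d)²

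With the stated inputs: 2 × 3.61 × (1.960 + 0.842)² / 0.7² = 7.22 × 7.85 / 0.49 ≈ 115.7, so 116 per arm. The noncentral t gives 117. The plan's figure is 50.

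**Step 2. Can another reading give 50?** Patients per arm for 80% power, noncentral t (normal approximation in brackets):

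| True difference | one-sided 0.025 | one-sided 0.05 |
|---|---|---|
| 0.3 against WI (as stated) | 117 (116) | 92 (92) |
| 0 | 58 (57) | 46 (45) |
| 0.3 in favour of WI (sign reversed) | 35 (34) | 28 (27) |

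No entry is 50. A two-sided superiority test for a 1-point difference needs 57 per arm (114 in total). To get 80% power from 50 per arm at d = 0.3, the SD would have to be 0.7 × √(50/2) / (1.960 + 0.842) ≈ 1.25, or about 1.41 at one-sided 0.05. The article states 1.9.

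**Step 3. Power the design has.** The standard error with 50 per arm is 1.9 × √(2/50) = 0.38. For d = 0.3 the normal approximation gives Φ(0.7/0.38 − 1.960) = Φ(−0.118) ≈ 45.3%. The noncentral t results are:

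| Evaluable per arm | True difference | one-sided 0.025 (95% CI) | one-sided 0.05 |
|---|---|---|---|
| 50 | 0.3 | 44.6% | 57.3% |
| 54 | 0.3 | 47.5% | 60.2% |
| 50 | 0 | 74.1% | 83.4% |
| 54 | 0 | 77.3% | 85.8% |

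**Step 4. The same result from the interval.** With 50 per arm the half-width of the 95% CI is t(98) × SE = 1.984 × 0.38 = 0.754. For the interval to stay within the margin, the observed difference must be below 1 − 0.754 ≈ 0.25. If the trial observed exactly the 0.3 that it expects, with SD 1.9, it would miss noninferiority.

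The step from 100 to 108 is 100 × 1.08; 100/0.92 would give 109. That difference is immaterial.

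**The case against.** The best case for the plan is that 100 can be traced to a slip. At one-sided 0.05 and no true difference, 46 per arm divided by 0.92 is 50.0 per arm, or 100 in total. At one-sided 0.05 and a difference of 0.3, 92 per arm divided by 0.92 is 100.0 per arm. So 100 may already include dropout, or may be a per-arm figure reported as a total. This is possible, and the article cannot settle it, but it does not rescue the text. The article calls the calculation two-sided, places the 100 before the dropout allowance, and says that the means were used. The per-arm reading also conflicts with 54 per arm.

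The 45% is conditional. It needs a true difference of 0.3, and the Background describes the group's earlier nonrandomized comparisons as showing no difference in pain control. If the arms are truly equal, power is 74.1% with the 95% CI. It passes 80% with 50 per arm only if the test is also relaxed to one-sided 0.05. This stands as a reason to state power for both differences.

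It is also fair that the article nowhere says a failed test would count in favour of L-TAP, so that misreading is a risk and not a stated plan. Finally, recruitment ended in March 2019, so the sample size cannot change. That limits the remedy, but the wrong figure would still inform how the result is read.

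**Conclusion.** The concern holds. On the article's own inputs (difference 0.3, SD 1.9, margin 1, two-sided 0.05), 100 evaluable patients give about 45% power, not 80%. About 117 per arm, 234 in total, would be needed for 80%. Full data on all 108 patients raises power only to 47.5%, and the most lenient test level that keeps the 0.3 difference gives 57.3% with 50 per arm and 60.2% with 54.

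Under the stated assumptions and the 95% CI, the trial is more likely to miss noninferiority than to show it. The figures assume normally distributed scores with a common SD and an unadjusted comparison of two means, as the named test implies. The origin of the 100 cannot be established from the article.

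**What to change.** 1. In Sample size calculation, withdraw the statement that 100 patients give 80% power. Replace it with wording such as: *With 100 evaluable patients (50 per arm), SD 1.9, a margin of 1 and a two-sided 95% CI, power is about 45% if WI is 0.3 points worse and about 74% if the arms are equal.* If the original software output shows other inputs, report them and say where they differ from those printed.
2. In the Abstract, replace the sentence that 54 per group are needed with one that gives 54 per group as the number planned, with the same conditional power or no power claim.
3. Add a sentence that failure to show noninferiority will be interpreted from the confidence interval and will not by itself be taken as evidence that L-TAP adds benefit. This is secondary to the correction of the figure.

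The cost is wording only. No patients are added and the analysis does not change, but the stated power becomes less favourable.

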### Allocation

Patients satisfying the inclusion criteria and willing to enter the study are randomized to one of the two study arms after signing the informed consent. The randomization is performed blindly in a 1:1 fashion. The allocation to WI group or WI plus L-TAP group is achieved by creating a randomization list that includes a maximum of six subjects for nine blocks. The randomization list has been obtained by using an online program available at https://www.sealedenvelope.com/simple-randomiser/v1/lists. A separate list has been created for each center so that 54 patients are recruited at the Division of General and Hepatobiliary Surgery, University of Verona Hospital Trust, Verona, Italy, and 54 patients at the Colorectal Cancer Center, Kyungpook National University Medical Center, Kyungpook National University, Daegu, Korea. Similarly, each center collects the data separately after identifying the patients with an alphanumeric code.

### Data collection and management

A trained member from each surgical staff is in charge of data collection. Baseline demographics, as well as preoperative, intraoperative, and postoperative variables, are collected using a specifically created datasheet and stored in a specifically created dataset. The same datasheet and dataset are used in the two centers (Additional file 2).

Furthermore, to reduce as much as possible the variability among patients in reporting pain intensity, the patient is instructed on use of the NRS by the same member of the surgical staff at the time of accrual (15–20 days before surgery) and the day before surgery. To reduce the variability related to data collection, the same member will collect all other investigated variables.

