## Methods/design

### Trial design

This is a prospective, randomized, controlled, two-arm, multicenter, single-blind study evaluating the efficacy of postoperative analgesic management of WI versus WI plus L-TAP in the context of laparoscopic colorectal surgery. Randomization is at the patient level, and participants are randomized 1:1 to receive either WI alone or WI plus L-TAP.

The protocol aim is to demonstrate the noninferiority of WI compared with WI plus L-TAP in terms of effectiveness of pain management. We are supposing a noninferiority limit for pain assessment measured according to the numeric rating scale (NRS) of 1 of 10 as the largest difference that is clinically acceptable, so that a difference in NRS greater than 1 would matter in practice.

Patients enrolled in this trial are asked to report their pain according to NRS at rest and during cough or movements, together with the occurrence of PONV at 6 h from surgery and twice daily until POD 3. Contemporarily, the amount of rescue analgesics is recorded, with patients being educated to request additional analgesic drugs when their pain is greater than NRS 4. Resumption of gut functions, evaluated as the passage of gas and stool as well as the ability to tolerate liquid and soft diet, is also considered together with the postoperative length of hospital stay. The study flow diagram and time of collection of outcomes are shown in Figs. 1 and 2, respectively.

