#### Interventional treatment

The study is based on the concept of preemptive administration of local analgesia so that both WI and L-TAP are carried out at the beginning of the surgical procedure.

The WI group contemplates the use of a total amount of 40 ml of 0.375% ropivacaine, splitting the dose (20 ml) at the trocar and minilaparotomy sites. The infiltration is completed before each skin incision.

The total amount of anesthetic in the WI plus L-TAP group is 60 ml of 0.25% ropivacaine. First, 10 ml are used to infiltrate the trocar sites. After the positioning of the trocars and the induction of the pneumoperitoneum, bilateral TAP block under laparoscopic guidance using the “two pops technique” is carried out using 20 ml of 0.25% ropivacaine for each side. Specifically, the camera is positioned for visualization of the lateral region of the abdominal wall, and an 18-gauge laparoscopic needle is introduced under direct vision at the center of the midaxillary line between the lower costal margin and the iliac crest until the surgeon feels a “pop,” after which the surgeon injects 2 ml of normal saline to verify the correct position. At this point, after Doyle’s internal bulge sign (the bulge created when the transversus abdominis muscle with peritoneum is pushed internally) is noted, the defined amount of local anesthetic is injected. The same technique is used for the contralateral block. The remaining 10 ml are injected before skin incision at the minilaparotomy site.

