### Outcome measures

#### Primary endpoint

To demonstrate the noninferiority of WI compared with WI plus L-TAP for pain control in the early postoperative period after laparoscopic colorectal resection. The pain control is evaluated at 6 hr from surgery considering the greatest intensity of pain at rest and during cough, according to NRS. The NRS is graded from 0 to 10, where 0 refers to “no pain” and 10 to “worst pain.”

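### One surgical-staff member per center handles both the operative data and the outcomes, so the person who appears to take the 6 h pain score can know the arm

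*Protocol article*

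**What the plan says.** The rule stands in the protocol article under Data collection and management. It opens: "A trained member from each surgical staff is in charge of data collection". The scope follows: "Baseline demographics, as well as preoperative, intraoperative, and postoperative variables, are collected using a specifically created datasheet". The same section gives this person the patient's training on the scale ("the patient is instructed on use of the NRS by the same member of the surgical staff at the time of accrual", and again the day before surgery) and closes with "To reduce the variability related to data collection, the same member will collect all other investigated variables".

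The primary endpoint is a 0 to 10 score: "The pain control is evaluated at 6 hr from surgery considering the greatest intensity of pain at rest and during cough, according to NRS". Trial design says that patients are asked to report their pain; it does not name who asks.

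On blinding, Trial design says "This is a prospective, randomized, controlled, two-arm, multicenter, single-blind study" without assigning the blind to anyone. The only other use of the idea is under Allocation, "The randomization is performed blindly in a 1:1 fashion", which concerns the randomization and not the assessment of outcomes.

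Interventional treatment shows how the arms differ in theatre. WI alone uses 40 ml of 0.375% ropivacaine by infiltration. WI plus L-TAP uses 60 ml of 0.25% and adds a bilateral block in which "an 18-gauge laparoscopic needle is introduced under direct vision at the center of the midaxillary line".

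**The concern.** A single collector per center is chosen to reduce variability, and it does reduce random differences between assessors. It does not protect against a systematic difference between arms when the collector knows the arm. The arrangement also brings the two kinds of information together: the record of the operation, where the technique is plain, and the outcomes.

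The trial is exposed to this because its main outcome is a subjective score obtained by asking, and its claim is noninferiority within 1 point. The planning difference between the arms is only 0.3 points (3.1 against 2.8), so a small arm-related shift in how scores are elicited or recorded would be of the same order as the difference expected. Some secondary outcomes call for judgment, notably prolonged ileus, whose definition turns partly on whether the expected course was impaired.

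**Working it through.** **Step 1: what the text implies about the collector.**

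- One surgical-staff member per center is in charge of data collection (stated).
- Intraoperative and postoperative variables are on the same datasheet, and both centers use the same sheet (stated).
- That member trains patients on the NRS and collects all other variables (stated). The 6 h NRS is a postoperative variable, so this member appears to record it. That is an inference: no sentence says who asks for the score.
- The operative information separates the arms by volume, concentration and the presence of the bilateral block (stated).
- No section masks the collector, keeps this person out of theatre or closes the operative record to them.

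Together, these points mean that the collector can know the arm. They do not show that the collector did.

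**Step 2: how much a shift would matter.** The protocol gives no figure for this, so there is nothing to reproduce. The following is an illustration.

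Inputs from Sample size calculation: SD 1.9 in each arm, margin 1, significance level 0.05 two-sided, 100 patients after dropout, hence 50 per arm. Assumed, not in the documents: a mean shift b in the recorded difference, taken as 0.2, 0.3 or 0.5 points. Also assumed: noninferiority is declared when the upper 95% limit for WI minus WI plus L-TAP is below 1, which is the usual rule when higher scores are worse. The wording of the boundary under Statistical analysis is a separate matter.

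SE = 1.9 × √(2/50) = 0.380.

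With true difference d and shift b in favour of WI, P(declare noninferiority) = Φ[(1 − d + b)/0.380 − 1.96].

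True difference at the margin (d = 1), where declaring noninferiority is an error:

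| Shift b (points) | Argument of Φ | P(false noninferiority) |
|---|---|---|
| 0.5 toward WI | −0.644 | 26.0% |
| 0.3 toward WI | −1.170 | 12.1% |
| 0.2 toward WI | −1.434 | 7.6% |
| 0 | −1.960 | 2.5% |
| 0.2 against WI | −2.486 | 0.6% |
| 0.3 against WI | −2.749 | 0.3% |
| 0.5 against WI | −3.276 | 0.05% |

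The opposite shift lowers the error but costs power. With no true difference (d = 0), power at 50 per arm is Φ(1/0.380 − 1.96) = Φ(0.672) = 74.9%. A shift of 0.2, 0.3 or 0.5 against WI reduces it to Φ(0.145) = 55.8%, Φ(−0.118) = 45.3% or Φ(−0.644) = 26.0%.

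With all 54 per arm, SE = 1.9 × √(2/54) = 0.366, and the error rates for shifts toward WI become 7.9%, 12.7% and 27.7%. The picture does not depend on the dropout assumption.

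**The case against.** The best case for the plan has four parts.

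*Knowledge of the arm is not shown.* The article does not say that the collector attends operations, that the technique is on the datasheet, or when intraoperative items are entered relative to the 6 h score. The datasheet is an additional file that is not shown. Patients carry an alphanumeric code, although nothing says that the code conceals the arm. This stands: the point is that the arrangement allows knowledge of the arm, and a reader who infers that the assessor was in fact unblinded goes further than the text.

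*The score is the patient's own.* An informed collector can act on the primary outcome only through how the question is put and how the answer is recorded. The outcomes that need judgment are secondary, and Statistical analysis describes their comparison by descriptive statistics and plots. This stands too, and it limits the likely size of the effect.

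*The direction is open.* A reader might infer that any bias favours noninferiority. The documents do not support that. The Background reports that the team's earlier nonrandomized studies found no difference in pain control, which could lead a collector to expect equal scores. The Discussion credits adding TAP block with good pain control and less opioid use, and the trial rationale suggests that preemptive block works better. Those expectations would push the other way.

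*Silence is not a finding.* A reader might also argue that needle marks on the flanks reveal the arm, or that the article fails by not naming the blinded party. Neither is a ground here. No section says that a mark is visible at 6 h or that a patient would understand it, and dressings and the identity of the blinded party are details that an article may leave to the full protocol.

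What survives is the stated rule. A fuller document could add masking, but the single-collector arrangement is fixed in this text, and its stated reason, lower variability, does not address bias that depends on a known arm.

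**Conclusion.** The point holds as a weakness of design that should be corrected, with moderate confidence. The protocol assigns operative and outcome data to one surgical-staff member per center and states nothing that separates the two, so the person who appears to take the primary score can know the arm.

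The size is conditional. If the recorded difference shifted by 0.2 to 0.5 points toward WI, the chance of a false noninferiority claim at the margin would rise from 2.5% to between about 8% and 26%. An equal shift against WI would instead make a true noninferiority harder to show. These shifts are assumptions, and nothing in the documents indicates that a shift of any size occurred. The conclusion also rests on reading the collector as the recorder of the 6 h NRS, which the text implies but does not state.

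**What to change.** Split the datasheet in two. The operating surgeon, already present at every case, completes the technique and intraoperative page, and that page stays closed to the collector until the 72 h scores are entered. The existing trained member stays out of the trial operations and records NRS, PONV, prolonged ileus and recovery without knowing the arm. This keeps the single collector that the protocol wants for consistency.

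The cost is a two-part form and no extra staff, provided the collector is not otherwise needed in theatre. The small downside is that the collector cannot assist at or observe trial operations.

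Trial status gives recruitment as completed on 31 March 2019, so the procedure can no longer be introduced for these patients. If a separation of this kind was already in place, the report should describe it. If it was not, the report should say whether the collector at each center knew the arm when the scores were taken, and qualify the noninferiority conclusion accordingly.

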### Statistical analysis

Statistical analyses will be performed on an intention-to-treat (ITT) basis using IBM SPSS Statistics software version 21.0 (IBM Corporation, Armonk, NY, USA). Because the ITT analysis includes all randomized subjects and, in this study**,** there may be up to 6% missing data, an imputation method will be established. A per-protocol (PP) analysis will also be performed. In noninferiority studies, both ITT and PP analyses are recommended and should support the noninferiority hypothesis. Continuous variables are summarized as mean and SD or as median and 95% confidence interval (95% CI) if the distribution is asymmetrical. Categorical variables are summarized as numbers and percentages. The categorical variables will be compared between groups with the chi-square test or Fisher’s exact test, depending on the number of events. The continuous variables will be compared between groups using an unpaired *t* test or the Mann-Whitney *U* test, depending on data representation. A two-sided *P* value less than 0.05 will be considered significant.

The primary outcome considers the level of pain at 6 hr from surgery graded according to the NRS. Assuming a pain score difference of 1 of 10 to be clinically significant, noninferiority is determined when the lower boundary of the 95% CI is > 1. Superiority, on the other hand, is determined when the two means are significant at the 5% level (two-sided *P* < 0.005).

The secondary objectives aim at assessing the benefits of choosing one procedure over the other. Descriptive statistics and plots will be used to compare the two groups, taking into account: (1) pain intensity scores at 12, 24, 36, 48, and 72 hr after surgery; (2) the quantity of rescue analgesic drugs consumed from the day of surgery until POD 3; (3) the occurrence of PONV; (4) the occurrence of PPOI; (5) the time needed to restore bowel function considered as the time needed to pass gas and stool as well as to tolerate a liquid and solid diet; and (6) the length of hospital stay.

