### Setting

Participants are recruited and operated on at the Division of General and Hepatobiliary Surgery, University of Verona Hospital Trust, Verona, Italy and at the Colorectal Cancer Center, Kyungpook National University Medical Center, Kyungpook National University, Daegu, Korea. One surgeon for each center will perform the totality of all procedures on enrolled patients. The annual caseload of laparoscopic colorectal resections for the two surgeons is approximately 200 patients.

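### Randomization is stratified by center, but the named tests for continuous variables ignore center, and the primary endpoint is not exempted from a data-dependent switch to Mann-Whitney

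*Protocol article*

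**What the plan says.** All references are to the protocol article.

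- **Allocation:** "A separate list has been created for each center so that 54 patients are recruited" at each site. Assignment is 1:1 in blocks within each list, so center is a stratification factor.
- **Setting:** "One surgeon for each center will perform the totality of all procedures on enrolled patients". Center and surgeon therefore coincide.
- **Statistical analysis, general rule:** "The continuous variables will be compared between groups using an unpaired *t* test or the Mann-Whitney *U* test, depending on data representation". On summaries: "Continuous variables are summarized as mean and SD or as median and 95% confidence interval (95% CI) if the distribution is asymmetrical". No section mentions a center term or a stratified comparison.
- **Statistical analysis, primary outcome:** "noninferiority is determined when the lower boundary of the 95% CI is > 1". The estimate to which this interval belongs is not named. The superiority rule, by contrast, refers to means: "Superiority, on the other hand, is determined when the two means are significant at the 5% level".
- **Primary endpoint:** "The pain control is evaluated at 6 hr from surgery considering the greatest intensity of pain at rest and during cough, according to NRS".
- **Sample size calculation:** "The noninferiority limit of NRS 1 has been intended to be the largest difference that is clinically acceptable". The calculation is for a difference of two means, with an SD of 1.9 in both groups.

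**The concern.** There are two linked problems.

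First, stratifying by center balances center across the arms, so center variation drops out of the true sampling variance of the arm difference. An unpaired t interval does not use this. Its pooled SD still contains the center difference, so the interval is too wide and noninferiority is harder to show than it need be. The two sites are in different countries, with different surgeons and different staff teaching the pain scale, so a center difference is plausible.

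Second, the margin is on the mean scale, but the general rule lets the data decide between a t test with means and a Mann-Whitney test with medians. The primary endpoint is not excepted. The planned means are 2.8 and 3.1 with SD 1.9 on a scale that stops at 0, so asymmetry is a realistic outcome. A standard Mann-Whitney test addresses equality of the arms and returns no mean difference to compare with 1 point.

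**Working it through.** **Inputs.** Margin 1, SD 1.9, planned difference 0.3 (3.1 − 2.8), two-sided 0.05 (one-sided 0.025), 100 evaluable patients: Sample size calculation. Two centers, equal numbers, 1:1 within center: Allocation. I take 50 per arm, 25 per arm per center. The center difference D is not in the documents; I assume 0 to 2 NRS points.

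**The plan's own figure.** n per arm = 2·SD²·(1.960 + 0.842)²/(margin − difference)².
- Difference 0.3: 2·3.61·7.85/0.49 = 115.7, so 116 per arm, 232 in total.
- Difference 0: 2·3.61·7.85/1 = 56.7, so 57 per arm, 114 in total.

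The stated 100 is not reproduced. That is a separate matter and the present point does not depend on it. It does show that there is little power to spare: at 50 per arm and a true 0.3, power is about 44% to 45% even with no center effect.

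**Effect of leaving out center.** Let s be the within-center SD. With n = 50 per arm:
- true SE of the arm difference = s·√(2/50) = 0.2·s
- SE used by the unpaired t interval ≈ 0.2·√(s² + D²/4)
- power ≈ Φ{[(1 − true difference) − 1.984 × SE used] / true SE}

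This takes noninferiority as the upper bound of WI minus WI plus L-TAP lying below +1. The direction printed in the rule is a separate matter.

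The article does not say whether 1.9 is a within-center or a total SD, so I take both readings.

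*1.9 as within-center SD.* True SE = 0.380. SE used = 0.393 (D = 1) or 0.429 (D = 2), so the CI is wider by √(3.61 + 0.25)/1.9 = 1.034 or √(3.61 + 1)/1.9 = 1.130. Worked case, D = 2, equal arms: unadjusted (1 − 1.984·0.429)/0.380 = 0.39, power 0.65; adjusted (1 − 1.985·0.380)/0.380 = 0.65, power 0.74.

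*1.9 as total SD.* At D = 2, s = √(3.61 − 1) = 1.616, true SE = 0.323, SE used = 0.380. Equal arms: unadjusted (1 − 1.984·0.380)/0.323 = 0.76, power 0.78; adjusted (1 − 1.985·0.323)/0.323 = 1.11, power 0.87.

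Simulation (40,000 runs per setting) agrees. Each cell gives unadjusted / center-adjusted:

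| Reading of 1.9 | D | Power, true 0 | Power, true 0.3 | One-sided error at the margin |
|---|---|---|---|---|
| either | 0 | 0.74 / 0.74 | 0.44 / 0.44 | 0.025 / 0.025 |
| within-center | 1 | 0.72 / 0.74 | 0.42 / 0.44 | 0.023 / 0.026 |
| within-center | 2 | 0.65 / 0.74 | 0.35 / 0.45 | 0.012 / 0.025 |
| total | 1 | 0.75 / 0.77 | 0.44 / 0.47 | 0.020 / 0.024 |
| total | 2 | 0.78 / 0.87 | 0.44 / 0.57 | 0.010 / 0.025 |

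The unadjusted error rate does not exceed 0.025 in any row.

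**The Mann-Whitney switch.** A nonsignificant Mann-Whitney P value cannot stand in for noninferiority. With scores rounded to 0–10, 50 per arm and a true shift of a full point, about 29% of simulated trials gave P > 0.05. Nor does skewness force the switch. With rounded 0–10 scores, skewness about 1.1 and SD about 1.9, the t interval covered 94.8% of the time and the one-sided error at the margin was 2.3%.

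**The case against.** **The primary outcome has its own rule.** Noninferiority is decided by a confidence bound against 1, superiority refers to means, and the sample size is for a difference of two means. The sentence on t and Mann-Whitney tests is general. A reader might infer that a Mann-Whitney P value will decide noninferiority, or that the primary question has no valid test. The documents do not say so, and that reading goes too far. A Hodges-Lehmann interval, or a rank test on data shifted by 1 point, could also address a shift of that size. What stands is narrower: the primary endpoint is not exempted, the estimate behind the interval is not named, the same section allows a median for skewed data, and neither rank-based device is mentioned.

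**Ignoring center is conservative.** This stands in full. A reader might infer bias or a risk of a false noninferiority claim; with 1:1 allocation within center there is neither.

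**The size is assumed.** This also stands. A center difference of 2 points exceeds one SD and is twice the margin, so a fall from 74% to 65% must not be read as the expected loss. If 1.9 is the total SD, unadjusted power does not fall below the no-center-effect level at equal arms; the loss is a gain forgone. The common datasheet and the repeated instruction in the pain scale (Data collection and management) are meant to limit variability. A reader might also suppose that length of stay and bowel recovery differ more between the hospitals; nothing in the article supports this.

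**A separate analysis plan could add center.** It could, but the article names the tests, and those named have no center term. This is a stated choice, not silence.

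**Conclusion.** The point holds as a loss of precision and an unsettled primary analysis, not as an error that threatens validity. The center term costs essentially nothing at D = 0. At 50 per arm it recovers about 2 percentage points of power at D = 1 and about 9 at D = 2 when the arms are equal, and about 3 and 10 to 14 points respectively at a true difference of 0.3. These figures rest on an assumed D, an SD of 1.9 and normally distributed scores. The Mann-Whitney part depends on no assumed figure: the margin is on the mean scale, and the text leaves open a primary analysis that is not. Both changes are worth making, since power at the planned difference is already low.

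**What to change.** State one primary analysis, fixed before outcome data are examined by arm: a linear model of the 6 h NRS with arm and center as factors. Report the adjusted mean difference (WI minus WI plus L-TAP) with its 95% CI against the 1-point margin, whatever the shape of the distribution. A bootstrap interval can serve as a check if the scores are skewed. Limit the choice between t and Mann-Whitney to other continuous variables, and keep Mann-Whitney for the primary endpoint as a supporting test only. Center adjustment of secondary comparisons is optional.

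The cost is a few lines of analysis wording and one extra factor in a model that the named software fits. No further patients or data are needed, and completed recruitment is no obstacle.
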